### Intention to treat

The data will be analysed according to intention to treat, although a subsequent per-protocol analysis will be carried out to check the stability of the conclusions. The multiple imputation procedure will be carried out in case of missing data.

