### Statistical analysis

Descriptive statistics (mean and 95% CI) will be reported at T0, T1 and T2 for all the variables. The distribution of data at baseline will be tested using the Shapiro-Francia tests. The baseline comparison between the three groups will be performed using the χ^2^ test for categorical variables and one-way analysis of variance (ANOVA) or the Kruskal-Wallis test for continuous variables, as appropriate. The outcome comparison between the three groups will be performed using a one-way ANOVA or Kruskal-Wallis test according to sample distribution. The intragroup comparison between T0, T1 and T2 will be performed using a t-test for paired data or a Wilcoxon test, depending on the distribution. In case of imbalances at baseline between the groups, appropriate statistical correction analyses (eg, analysis of covariance) will be adopted. Patient perspectives on the acceptability and usability of the robot intervention will be analysed using descriptive analysis for quantitative and inductive content analysis for qualitative data.^56^

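### If data are missing and the normality check selects rank tests, the planned multiple imputation yields several p-values that Rubin's rules cannot combine directly; one baseline-adjusted, estimate-based analysis of T25-FW would avoid this

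*Protocol article*

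**What the plan says.** The section on intention to treat fixes the analysis set (all participants as randomised, with a per-protocol analysis afterwards as a stability check) and the missing-data method: "The multiple imputation procedure will be carried out in case of missing data".

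The statistical analysis section fixes the tests. Between groups: "The outcome comparison between the three groups will be performed using a one-way ANOVA or Kruskal-Wallis test according to sample distribution". Within groups: "The intragroup comparison between T0, T1 and T2 will be performed using a t-test for paired data or a Wilcoxon test, depending on the distribution". Baseline adjustment is conditional: "In case of imbalances at baseline between the groups, appropriate statistical correction analyses (eg, analysis of covariance) will be adopted". Summaries are estimate-based: "Descriptive statistics (mean and 95% CI) will be reported at T0, T1 and T2 for all the variables".

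The sample is 24, with 8 per arm. The article does not say how results from imputed datasets will be combined, and it does not say that Rubin's rules will be applied to rank tests.

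**The concern.** Multiple imputation gives one inference because each completed dataset supplies an estimate and a variance, which Rubin's rules combine. Kruskal-Wallis and Wilcoxon, as usually reported, supply neither. On that branch the analyst holds a set of p-values and must choose a way to reduce them to one. With 8 per arm, one missing value is 12.5% of an arm and two are 25%, so the imputed sets can fall on different sides of 0.05 and the choice of rule can decide the result.

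Both conditions are realistic. T25-FW is a time measured in people with EDSS 6 to 7, where skew is plausible. There is a 3-month follow-up, and participants who miss more than three sessions leave the study. The discussion expects significantly greater change in one arm, so a between-group test will carry weight.

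**Working it through.** The article gives no power, alpha or dropout figure to reproduce. The check sets the two sections side by side and then measures how much the pooling rule matters.

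**1. Which planned analyses can be pooled**

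Rubin's rules: pooled estimate = mean of the m estimates; total variance T = W + (1 + 1/m)B, where W is the mean within-imputation variance and B the between-imputation variance.

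| Planned analysis | Estimate and SE for Rubin's rules? |
|---|---|
| Means with 95% CI | Yes |
| Paired t-test | Yes |
| One-way ANOVA, ANCOVA | Yes, through the group contrasts |
| Kruskal-Wallis | No; H statistic and p-value only |
| Wilcoxon | Not as usually reported |

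**2. A valid route on the rank branch**

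The D2 rule pools chi-square-type statistics. For Kruskal-Wallis H on k = 2 df:

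- r = (1 + 1/m) × var(√H)
- D2 = [mean(H)/k − ((m+1)/(m−1)) r] / (1 + r)
- reference distribution F(k, ν), with ν = k^(−3/m) (m−1)(1 + 1/r)²

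With m = 5 the constants are 1 + 1/m = 1.2, (m+1)/(m−1) = 6/4 = 1.5, and ν = 0.66 × 4 × (1 + 1/r)² = 2.64(1 + 1/r)².

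For the paired Wilcoxon comparison, a Hodges-Lehmann estimate with a standard error derived from its rank-based interval can be pooled by Rubin's rules. One simulated example gave −0.59 (SE 0.095).

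**3. Size of the difference between rules**

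From the article: three arms of 8. Assumed: correlation 0.8, two-sided 5% test, normal imputation on arm and baseline, Kruskal-Wallis on change, values missing at random or completely at random, no true effect. Ranges cover separate runs of 2,000 or 3,000 trials with m = 5. The Monte Carlo SE at 5% is √(0.05 × 0.95/3000) = 0.4 points for 3,000 trials.

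| False-positive rate | 1 missing per arm | 2 missing per arm |
|---|---|---|
| D2 | 4.2–4.3% | 5.6–5.8% |
| Median p-value | 6.9–7.1% | 11.1–12.0% |
| Any imputed set significant | 12.4–12.8% | 25.6–26.4% |
| All sets stacked | 61–62% | 64–65% |

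Complete data gave 3.8–5.0%. With 2 missing per arm the five sets disagreed on significance in 22–23% of null trials, and in 43% at an effect of 1 residual SD.

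With m = 20 and 2, 3 or 5 of 24 missing in total (1,500 trials each), D2 rejected in 4.1%, 4.1% and 4.2% of null trials and the median p-value in 7.1%, 7.1% and 8.6%. The imputed p-values straddled 0.05 in 11%, 18% and 31%.

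**4. What the alternative model gives**

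A baseline-adjusted model on observed data kept about 5% error. At an assumed effect of 1 residual SD its power was roughly 35–39%, against 16–18% for an unadjusted Kruskal-Wallis test on post-treatment values.

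Most of that gain comes from using baseline. With unit variance and correlation 0.8, the SD given baseline is √(1 − 0.64) = 0.60, the SD of change is √(2 × 0.2) = 0.63, and the SD of raw post-treatment values is 1.0. An effect of 0.60 is therefore 1.00, 0.95 and 0.60 SD respectively. If the group comparison is made on change, the power gain would be much smaller. The article does not say which is used.

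**The case against.** A reader might infer that the intention-to-treat analysis has no valid result once data are missing. The documents do not support this. D2 is an established rule and holds its level here, and the Wilcoxon comparison can be pooled through a Hodges-Lehmann estimate. The difficulty also needs two conditions together: missing data and a distribution check that selects the rank branch. All the other planned analyses pool by standard rules.

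A reader might also count the unnamed pooling rule as an error. It is not. A condensed article may leave the pooling rule, imputation model and number of imputations to a fuller document. The stacked and any-set figures show what misuse would do; the article proposes neither, nor the median p-value.

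How often the rank branch would be used is unknown. For lognormal times with an assumed log-SD of 0.3 to 0.7, a 5% Shapiro-Francia test rejects normality in about 10–29% of single arms of 8, and in 28–81% of samples if all 24 are tested together. The trial is also a pilot that disclaims definitive conclusions.

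These points stand and limit the scope. They do not remove the mismatch: the article has fixed both the test family and the missing-data method, and on one branch they join only through a special rule or a change of test.

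**Conclusion.** The point holds for the rank-test branch with missing data, and only there. On that branch the article's text does not determine a single result, and the rule chosen matters: about 4–6% error with D2 against about 7–11% with the median p-value at 1 to 2 missing per arm and 5 imputations. These sizes rest on the assumed correlation of 0.8, normal imputation, the missingness shares and the use of change as the outcome, none of which the article gives. For a pilot of 24 this is a modest weakness. It merits a change because a better and cheaper analysis is already half named in the plan: ANCOVA, at present reserved for baseline imbalance.

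**What to change.** For T25-FW, prespecify one estimate-based analysis whatever the normality test shows:

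- Regress log time at T1 (and at T2) on arm with log T0 as covariate, either as ANCOVA at each visit or as a mixed model over visits with arm, visit and arm-by-visit terms and a small-sample df correction.
- Adjust for baseline always, not only when imbalance is seen.
- If multiple imputation is kept, fit this same model in each imputed dataset and pool by Rubin's rules.
- Keep rank tests as a sensitivity analysis on observed data or, if they are to be run on imputed data, state that Kruskal-Wallis is pooled by D2.

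A smaller change, naming D2 for the Kruskal-Wallis branch, would close the between-group pooling gap but would leave the test dependent on the distribution check and baseline adjustment conditional.

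The cost is a few lines of text and no new data. The downside is reliance on approximate normality of residuals on the log scale, which residual plots and the rank-based sensitivity analysis can check.

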### Data monitoring and interim analysis

The study does not have a data monitoring committee. The research coordinator will conduct an interim analysis every 6 months to determine whether the study should be stopped, modified or continued. Any subsequent changes will be discussed by the research team and communicated to the funding agency and the ethics committee.

## Discussion

This pilot randomised controlled trial aimed to investigate the efficacy of robot-assisted gait rehabilitation in PwMS by identifying the robotic intervention’s loading factors, related metabolic response and the patient’s perspective. Identifying these non-operator-dependent intervention models would optimise the use of RAGT in future research studies and clinical practice.

We expect this study to observe an improvement in gait, mobility and balance in all patients, both those who received robot-assisted gait rehabilitation and those who received OGT. However, considering the results of increasing training intensity in other populations,^16 19 23^ we expect significantly greater changes in subjects assigned to the low-intensity RAGT at progressively increasing intensity group than in the other treatment groups.

Identifying the optimal dose response could be useful in PwMS, where fatigue management must be considered when defining the rehabilitation intervention and its parameters. The novelty of the intervention we will apply lies in proposing a low-intensity intervention and gradually increasing its intensity throughout the treatment sessions. This approach seems in contrast to literature recommendations regarding exercise characteristics that must be intense and high doses to promote learning mechanisms and neuroplasticity.^57 58^ The idea that more is better may not be suitable for a patient in whom symptoms like fatigue and spasticity caused by high-intensity training may compromise the effectiveness and applicability of the intervention, particularly in patients with a high disability level. Furthermore, implementing a low-intensity protocol would broaden the range of PwMS who can benefit from robotic gait therapy.

Concerning exosomal urinary miRNAs, we expect to identify one or more miRNA correlated with MS to confirm that urine is a useful body fluid for detecting molecules related to this pathology. We also expect to be able to establish one or more miRNA panels to be used as diagnostic/prognostic biomarkers of the effects of treatments, regardless of the intervention.

Psychiatric comorbidities represent a challenge when treating patients with PwMS due to the high prevalence of these disorders and the limited evidence for the efficacy of pharmacological treatments.^59^ On the other hand, there is emerging evidence about the effectiveness of rehabilitation programmes on mood symptoms in MS patients.^60^ Consequently, we anticipate that participation in rehabilitation treatments will yield positive outcomes for all patients, irrespective of their group allocation. However, variations in the exercises’ content across the three groups, particularly in intensity, are expected to elicit distinct experiences, perceptions and emotional responses from the patients, contingent on the nature of their assigned intervention.

We assume that both quantitative and qualitative data on the usability and acceptability of the robotic intervention will provide valuable insights into the patient’s ‘lived experience’.^61^ Qualitatively exploring the unique perspectives of PwMS and severe gait disability and collecting their suggestions regarding possible barriers and strategies for participation might inform future intervention implementation.^62^ Since RAGT is safe and well tolerated by patients with MS,^63^ we expect patients to provide positive feedback on the robotic intervention.

Our study may have some limitations. First, the pilot nature of the study does not allow any definitive conclusions due to the low number of subjects recruited. Second, the absence of a follow-up evaluation of more than 3 months does not allow us to conclude the effectiveness of the low-intensity intervention at progressively increasing intensity over time.

If the pilot study’s findings confirm our hypothesis, a randomised trial on a larger group of subjects would allow us to confirm our results.

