### Aims of the study

The study’s primary aim is to test whether the variability of response to RAGT in PwMS might be related to the imposed load factors and the consequent metabolic response.

The secondary aims are to investigate MS progression and response to rehabilitation treatment through the study of urinary miRNA and to collect information about the usability, acceptability and perceived pleasantness of new rehabilitative technologies in gait training from the patient’s perspective.

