#### Laboratory-based measures

Exosomes purification from urine. Urine (20–50 mL) of patients at T0 and T1 will be collected in the morning and stored at 4°C until purification of urinary exosomes (uEVs) after the addition of protease inhibitors. Urine samples from each patient will be centrifuged at 2000×g for 30 min at 4°C to remove cells, cellular debris, bacteria and apoptotic bodies, then at 17 000×g at 4°C for 60 min to remove remaining macropolymers and large extracellular vesicles. The supernatant will then be subjected to ultracentrifugation at 200 000×g for 60 min at 4°C. The resulting pellet, corresponding to the exosomal fraction, will be resuspended in 250 µL of PBS and stored at −80°C.^52^
Analysis of miRNA expression in urinary exosomes: Total RNA will be extracted from uEVs using the miRNeasy Micro Kit (Qiagen, Hilden, Germany) following procedures previously described in the literature.^53 54^ Reverse transcription to cDNA will be performed using the miRCURY LNA RT Kit (Qiagen). According to the manufacturer’s instructions, the ‘Urine Exosome Focus miRNA’ PCR panel (Qiagen) will be used for miRNA profiling. The panel allows the analysis of the expression of 87 urinary miRNAs, variably correlated with neurogenesis, activity of nerve cells and/or cardiovascular system. The panel also includes five miRNAs to be used as normalisers for calculating the expression levels of exosomal miRNAs using the 2^−∆∆Ct^ method.

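### The urinary miRNA aims ask for correlation with MS and for MS progression, which an all-MS sample with urine taken only around a 4-week programme cannot show; one or more hits among 87 is weak evidence

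*Protocol article*

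**What the plan says.** Aims of the study: a secondary aim is to "investigate MS progression and response to rehabilitation treatment through the study of urinary miRNA".

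Laboratory-based measures: urine "of patients at T0 and T1 will be collected in the morning", and the schedule in Table 1 agrees, with no laboratory sample at T2. On the number of markers: "The panel allows the analysis of the expression of 87 urinary miRNAs". On normalisation: "The panel also includes five miRNAs to be used as normalisers". Expression is computed by the 2^−ΔΔCt method, which is a relative measure.

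Statistical analysis: "The outcome comparison between the three groups will be performed using a one-way ANOVA or Kruskal-Wallis test according to sample distribution". Within groups: "The intragroup comparison between T0, T1 and T2 will be performed using a t-test for paired data or a Wilcoxon test". The section gives no significance level and no multiplicity rule for any outcome, and no method specific to the miRNA panel.

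Discussion: "we expect to identify one or more miRNA correlated with MS to confirm that urine is a useful body fluid". The same paragraph goes on to expect one or more miRNA panels that would serve as diagnostic or prognostic markers of treatment effects, whichever intervention was given.

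**The concern.** The claims expected from the miRNA work and the design that is to deliver them do not match.

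- A marker correlated with a disease has to differ between people with and without it, or at least follow a gradient of it. The selection criteria admit only people with progressive MS in a narrow disability band, so neither contrast is properly available.
- Progression has to be followed over time. The two urine samples lie about 4 weeks apart, on either side of a treatment meant to improve walking.
- The expectation is met by a single miRNA out of 87, and that single finding is said to confirm that urine is useful. With so many markers, a few nominal hits are expected when nothing is there.

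At stake is the conclusion on a stated secondary aim. Chance findings, or changes that merely accompany the passage of time, could be reported as MS markers and carried into later work.

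**Working it through.** The article gives no alpha, power or error rate for the miRNA screen, so there is no figure of its own to reproduce. The check has two parts.

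**Part 1: design against claim.**

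| Claim | What it needs | What the article provides |
|---|---|---|
| miRNA correlated with MS | A non-MS comparison, or a wide range of disease severity | MS is an inclusion criterion; EDSS 6 to 7 only; no non-MS samples described |
| MS progression through miRNA | miRNA related to the course of disease over time | Urine at T0 and T1, around 4 weeks of treatment; EDSS used at entry and not listed as an outcome; T25-FW at T0, T1 and T2 |
| Change regardless of intervention | An untreated reference | All three arms receive active rehabilitation |

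The first row cannot be met. The second can be met only in a limited way: miRNA at T0 or T1 can be related to T25-FW up to T2. T25-FW is, however, also what the training is meant to change. In the third row, a pooled T0–T1 change cannot be told apart from time or regression to the mean.

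**Part 2: how often would one or more of 87 be found with no true signal?**

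Inputs: m = 87 miRNAs (Laboratory-based measures). The five normalisers may lie inside or outside the 87, so m = 82 was also run. There are 24 patients, 8 per arm (Sample size calculation). The two-sided alpha of 0.05 per test, unadjusted, is an assumption; the 95% confidence intervals planned for the descriptive statistics merely suggest it.

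- Expected false positives, m × alpha: 87 × 0.05 = 4.35; 82 × 0.05 = 4.1.
- Chance of at least one under independence, 1 − (1 − alpha)^m: 1 − 0.95^87 = 98.8%; 1 − 0.95^82 = 98.5%.
- A T0–T1 test in each of three arms: 3 × 87 × 0.05 = 13.05 expected.
- At other alphas, m = 87 under independence: 58.3% at 0.01 and 8.3% at 0.001. At 0.05/87 = 0.00057 it is 4.9%.

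Independence is unlikely, if only because every miRNA is scaled to the same normalisers. Simulating 87 null markers with equal pairwise correlation (1,500 runs per cell, p < 0.05) gives the chance of at least one hit:

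| Correlation | Paired t, n = 24 | Paired t, n = 8 | ANOVA, 3 × 8 |
|---|---|---|---|
| 0.2 | 95.9% | 97.3% | 97.1% |
| 0.3 | 92.5% | 94.1% | 91.9% |
| 0.5 | 76.5% | 78.9% | 74.7% |
| 0.7 | 48.7% | 56.5% | 51.3% |
| 0.9 | 24.3% | 26.4% | 24.5% |

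The expected count does not depend on correlation; the simulated means scatter around 4.35 (3.78 to 4.79).

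**The case against.** The strongest reply is that this is an exploratory component of a pilot, described in a condensed article. Several stronger readings are tempting, and the documents do not support them.

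- *There is no error control.* The article states none, but it states none for any outcome, and an analysis plan that is not shown may contain a rule. Silence is not the defect. The 0.05 used above is an assumption about how the tests might be run.
- *A false hit is near certain.* That needs unadjusted 0.05 tests and weak correlation. At a correlation of 0.7 the chance is about half, and at 0.9 about a quarter.
- *One or more is a success criterion.* It is an expectation in the Discussion. The aim itself is to investigate, and no decision rule is attached.
- *Without people free of MS, nothing can be diagnostic.* The diagnostic or prognostic wording concerns treatment effects, so the missing comparator does not by itself defeat it. What 24 patients without a validation set cannot do is establish a panel ready for use.
- *Progression is unobservable because EDSS is not repeated.* The article treats T25-FW as an indicator of current and future disability and measures it to T2, so some exploration is possible.

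The article also concedes that a pilot of this size allows no definitive conclusions and that a larger trial would be needed. That caveat covers low numbers and short follow-up. It does not cover the missing comparator or the two-point urine sampling, and a larger trial of the same design would still be unable to show correlation with MS. The mismatch therefore stands, and an analysis plan could not remove it without changing the claims.

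**Conclusion.** The point holds as a mismatch between claim and design. Correlation of a miRNA with MS cannot be shown in this trial. MS progression is not supported as an aim beyond an exploratory link between miRNA at T0 or T1 and walking function up to T2. This conclusion needs no numerical assumption.

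The multiplicity part is conditional. If all 87 miRNAs were tested unadjusted at 0.05 and none had a true signal, 4.35 hits would be expected whatever the correlation. At least one would appear with probability 98.8% under independence, about 75–79% at a pairwise correlation of 0.5 and 49–57% at 0.7. Over most of that range, finding one or more says little about whether urine is useful.

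**What to change.** - Restate the secondary aim as exploratory: change in urinary miRNA from T0 to T1 within people with MS, and its association with change in T25-FW.
- Delete the progression wording from the Aims, and the expectation of MS-correlated miRNA as confirmation from the Discussion.
- Where the Discussion expects to establish panels for use as biomarkers, say instead that candidates will be identified for validation.
- Apply a false-discovery-rate procedure over all miRNAs tested, with the level fixed in advance, and report how many were tested. If the analysis plan already has such a rule, cite it.
- Keep the randomised between-group comparison. State that a pooled T0–T1 change cannot be separated from time, because every arm receives active rehabilitation, and so is not a treatment effect.

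No new patients, visits or samples are needed. The price is fewer declared miRNAs and a more modest claim. With n = 24, a correlation of about 0.40 passes p < 0.05 (t = 2.074 on 22 df; r = t/√(t² + 22)). A lone hit under, for illustration, a 10% false-discovery rate needs p ≤ 0.10/87, or about 0.62 (t = 3.73). For paired change at the strictest level, 0.05/87, power with all 24 pooled is 9.8%, 49% and 79% for assumed standardised changes of 0.5, 0.8 and 1.0; unadjusted it is 65%, 96% and 99.7%. Within one arm of 8 at 0.05/87 it is 0.6%, 2.5% and 5.3%. The article gives no effect sizes, so these are illustrations.
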